**Methods:** This 6-month study will adopt a one-arm mixed method type 3 implementation-effectiveness hybrid design and be conducted in a single clinical site, the Chronic Viral Illness Service of the McGill University Health Centre. It will be guided by tools of implementation science (e.g., frameworks, outcomes). Five HIV physicians and 30 of their HIV patients will participate. The intervention will involve having patients complete the I-Score with an adapted version of the Opal smartphone app, prior to meeting with their physician. Both the patient and the physician will have access to the I-Score results, for consideration during the clinic visits at Time 1 (T1), T2 (3 months), T3 (6 months). The implementation strategy will focus on patient and provider involvement, education, and training, as well as on promoting the intervention's adaptability. The strategy's cornerstone will be the hiring of an Application Manager to facilitate implementation. Implementation, patient, and service outcomes will be collected (T1, T2, T3). The primary outcome of this pilot study is the intervention's acceptability (target: mean scale score of 4 on 5). Qualitative data obtained through provider focus groups (T2, T3), patient interviews (T2, T3) and the Application Manager's field notes (T1-3) will serve especially to evaluate the implementation strategy and inform any methodological adaptations.

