### *The I-Score intervention*

During the study, participating patients will visit with their HIV physician three times, at Time 1 (T1), month 3 (T2), and month 6 (T3), prior to which they will complete the I-Score, as instructed. This visit schedule was selected as it fits within guidelines for the clinical follow-up of HIV in Quebec (Ministère de la santé et des services sociaux, 2019), while maximizing the collection of repeated study measurements. Given COVID-19, one visit (T2) will be done remotely (by phone or teleconferencing), while the other visits will be held at the CVIS. The I-Score PROM contains 20 items, covering 6 domains of barriers to ART adherence. Respondents indicate how often each barrier made adherence difficult in the past 4 weeks, with a continuous scale, from never to always. [Additional details on measure scoring and interpretation will be provided to the REB as they become available]. For details on the measure's development see Engler et al., 2018, Engler et al., 2019, Lessard et al., 2019, Toupin et al., 2018.

The core intervention of this pilot consists of having individuals with HIV on ART register on the Opal app and complete the I-Score PROM prior to each of three consecutive visits with their HIV physician. The patients will receive a reminder to complete the I-Score one week before their visit and they will have immediate access to their results. The HIV physician will acquire the I-Score results before each visit via the ORMS dashboard, an appointment and questionnaire management tool integrated with Opal and designed specifically for healthcare providers. The option of graphically presenting scores over time will also be available, allowing physicians and patients to compare past and present scores. It is expected that patients and physicians will review the I-Score results so they can be considered during the clinic visit (see Figure 1).

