### **Objective 3 -Determine preliminary intervention and effectiveness outcome utility**

This pilot study will collect data on one service outcome, patient management. It will be verified with a checklist submitted to participating physicians to allow them to record, per patient encounter, if they received the I-Score results on time, if they reviewed them prior to or during the clinic visit, if they were discussed during the visit, and if the I-Score identified concerning barriers. Then, they will check off any clinical actions that were taken based on the I-Score results or any related patient-provider discussion (e.g., recording issues in medical notes, referring to another health professional, ordering a test, changing a medication or treatment, providing advice or education). See the Appendix for the physician checklist.

The patient outcomes assessed in this pilot are barriers to adherence, adherence and viral load. Barriers to ART adherence will be assessed at T1, T2, and T3, with our previously described ePROM. Adherence will be examined with the Self-Rating Scale Item (SRSI) (Feldman et al., 2013) at T1, T2, and T3. It is a one item measure of treatment adherence (i.e. “Rate your ability to take all your medications as prescribed” [over the past 4 weeks], rated on a 6-point scale (i.e. Very poor, Poor, Fair, Good, Very good, and Excellent). Viral load, a clinical indicator of viral activity (e.g., infectiousness) and treatment response, will be treated as a dichotomous variable based on whether, as indicated in the patient’s medical file, the HIV RNA viral load is detectable (over 50 copies), or not. Undetectability is a goal of HIV treatment. The most recent viral load test result at T1 and T3, will be collected.

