## **Data analysis**

### **Quantitative analysis**

Time 1 questionnaires for people living with HIV and for HIV physicians will be summarized with descriptive statistics. For continuous variables, the minimum, the maximum, the mean, and the standard deviation will be reported. For ordinal and nominal qualitative variables, we will report absolute and relative frequencies (proportions).

As, specified, for most quantitative metrics relating to Objectives 1 and 2, as recommended for pilot studies, score targets were set to evaluate the ability to proceed to a definitive trial (Thabane et al., 2010). For people living with HIV and HIV physicians, continuous outcomes expressed on a Likert scale will be summarized with the minimum, the maximum, the mean, and the standard deviation at T1, T2 and T3. Binary outcomes (yes or no) will be reported with absolute and relative frequencies (proportions) at T1, T2 and T3. The means and proportions of T1, T2 and T3 will be confronted with their corresponding thresholds for success, presented in Table 2. To study the tendency of means and proportions for people living with HIV over time, a Linear Mixed Model (LMM) or a

Generalized Linear Mixed Model (GLMM) will be used, for continuous and binary outcomes, respectively. The response variable of each model will be the corresponding outcome and the independent variable will be the time (T1, T2 and T3). The null hypothesis of no time effect on the corresponding outcome will be tested with a Student's t-test on the regression coefficient. If the null hypothesis is rejected, we will perform post-hoc Student's paired t-tests between all combinations of time points to show between which time points means and proportions differed significantly. Additionally, to verify if each threshold for success is met at the end of the study, we will test the null hypothesis that each mean or proportion at T3 is inferior to its corresponding threshold with a Student's t-test. For all analyses, a significance level of 5% will be adopted. Finally, where appropriate, Cronbach's alpha will be calculated to evaluate the internal consistency of subscales.

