Regarding the patient outcomes of Objective 3, barriers to adherence and adherence will be summarized with the minimum, the maximum, the mean, and the standard deviation. Viral load will be reported by absolute and relative frequencies, as it is considered a dichotomous variable. For the service outcome obtained from the physician checklist, we will report the proportion of clinic visits when physicians took action based on the I-Score results, among the visits where an adherence barrier of concern was identified by physicians. Proportions will be reported for T1, T2 and T3 and globally, across time periods. To evaluate evidence of a statistically significant difference in our chosen effectiveness outcomes, we will run a Student's paired t-test for barriers to adherence and adherence and a McNemar test for viral load, between T1 and T3. To complete the analysis of the service outcome, we will use a logistic regression model, considering only the visits where an adherence barrier of concern was identified by physicians. The dependent variable is the binary variable of whether or not an action was taken by physicians and the independent variable is the time, considered as a factor with three independent levels (T1, T2 and T3). We will test the null hypothesis that time has no effect on the probability of taking action, with a t-test on the regression coefficient. We will conclude the analysis by testing the null hypothesis of equality of proportions between all pairwise combinations of time points, with a Student's t-test between two proportions, performing a Bonferroni correction for multiple tests. For all analyses, a significance level of 5% will be adopted.

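### The service-outcome analysis ignores repeated visits by the same patients and physicians, and tests a three-level time factor with a single coefficient

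*Protocol*

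**What the plan says.** The outcome comes from a checklist that physicians fill in, "to allow them to record, per patient encounter" (Protocol, Objective 3). The data structure is stated in two places: "Five HIV physicians and 30 of their HIV patients will participate" (Summary), and "participating patients will visit with their HIV physician three times, at Time 1 (T1), month 3 (T2), and month 6 (T3" (The I-Score intervention).

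The analysis is in Quantitative analysis: "we will use a logistic regression model, considering only the visits where an adherence barrier of concern was identified by physicians". Time is the only covariate: "the independent variable is the time, considered as a factor with three independent levels (T1, T2 and T3". The null hypothesis is that "time has no effect on the probability of taking action, with a t-test on the regression coefficient". The section ends by "testing the null hypothesis of equality of proportions between all pairwise combinations of time points", using a two-proportion t-test with Bonferroni correction.

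Table 3 gives p ≤ 0.05 as the threshold for success for this outcome. It does not say which of these p-values is meant.

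For Objectives 1 and 2 the same section plans linear or generalized linear mixed models for patients' outcomes over time. There too a single coefficient carries the test: "The null hypothesis of no time effect on the corresponding outcome will be tested" with a t-test on the regression coefficient. For the other Objective 3 outcomes the section plans paired t-tests and a McNemar test.

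**The concern.** Two things do not fit together.

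- **Dependence.** The same patient can contribute up to three visits, and each physician makes the decision at many visits. Plain logistic regression and unpaired tests of proportions assume independent visits. The protocol respects repeated measurement for its other repeated outcomes, so this one is the exception.
- **Degrees of freedom.** The hypothesis concerns three time points, which means two free parameters. The named test concerns one.

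What is at stake is the p-value compared with Table 3. The section Study metrics and instruments says that a missed threshold means modification before a definitive trial. An invalid p-value could therefore feed a stated progression rule. The model, coding, test and pairwise procedure are all written into the protocol, so this is a stated rule that does not work and not a detail left for later.

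**Working it through.** The protocol gives no power, action rate, number of concern visits or correlation for this analysis, so there is no figure of its own to reproduce.

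**1. Structure.** 30 patients × 3 visits = at most 90 visits. With 5 physicians that is 90/5 = 18 visits each if patients are spread evenly (an assumption). Only visits with a barrier of concern enter the model.

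**2. One coefficient against a 2-df hypothesis.** With T1 as reference:

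logit(p) = β0 + β2·[T2] + β3·[T3]; no time effect means β2 = β3 = 0.

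A t-test on one coefficient examines β2 = 0 or β3 = 0, not both. Take action rates 0.50, 0.50 and 0.85, with 20 independent concern visits per time point:

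- β2 = 0, so the T2 coefficient can reject only by chance: about 4% of runs.
- β3 = ln(0.85/0.15) = 1.73. At expected counts its SE = √(1/10 + 1/10 + 1/17 + 1/3) = 0.77, so z is about 2.25. It rejects in about 64% of runs.
- The joint 2-df Wald test rejects in about 64%.

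These rates are among the 96% of runs in which no time point is all-yes or all-no (0.85^20 = 0.039). The answer thus depends on which coefficient is read, and the protocol does not say.

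**3. Effect of ignoring dependence.** For a difference between two time points,

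Var(p̂3 − p̂1) = Var(p̂3) + Var(p̂1) − 2·Cov(p̂1, p̂3).

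Stable differences between patients or physicians make the covariance positive. The unpaired analysis drops it, so its SE is too large. If physicians shift differently from one time point to the next, all visits to a physician at that time move together. The analysis leaves that variance out, so its SE is too small.

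Simulation under no time effect used 4,000 trials per scenario, with 5 physicians × 6 patients × 3 visits. Each visit was of concern with probability 0.5, 0.8 or 1. All SDs are on the logit scale and are assumptions. Results at a median action rate of 0.5, nominal 5%:

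| Scenario | Rejection, one coefficient |
|---|---|
| No clustering | 3.8–5.7% |
| Stable patient or physician effects (patient SD 1–3, physician SD 0–1) | 0.4–3.1% |
| Physician-by-time SD 1, patient SD 1, physician SD 0–1 | 6–12% |

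In the last scenario a joint test that ignores clustering rejects in 5–14%, so moving to 2 df does not by itself cure the clustering. At a median action rate of about 0.73, stable effects give 0.5–2.5%. At a median rate of about 0.9, even the physician-by-time scenario stays at or below about 6%, because the Wald test becomes conservative there.

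**4. Separation.** With m independent concern visits per time point and action probability p, the chance that some time point is all-yes or all-no is 1 − (1 − p^m − (1 − p)^m)^3.

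| m | p = 0.5 | 0.7 | 0.8 | 0.9 | 0.95 |
|---|---|---|---|---|---|
| 10 | 0.6% | 8% | 29% | 72% | 94% |
| 15 | 0.0% | 1.4% | 10% | 50% | 85% |
| 30 | 0% | 0% | 0.4% | 12% | 52% |

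**The case against.** The strongest reply is that little hangs on this test. Objective 3 is secondary, the design is meant to observe effectiveness rather than test it, and Quantitative analysis ties the targets for proceeding to Objectives 1 and 2. That limits the weight of the point. It does not remove it, because Table 3 lists a p-value threshold for this outcome.

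A second reply is that the mixed models are planned only for patients' outcomes, while this one is a physician checklist. That explains the difference but does not justify it, since every checklist belongs to one patient and one physician.

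A reader might also infer more than the documents support:

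- **That the model will often not be estimable.** No action rate or number of concern visits is given. Action is defined broadly (a chart note or advice counts), so high rates are plausible, but the risk runs from near 0% to above 90% across the assumed range.
- **That equality over time is never tested.** The three Bonferroni-corrected pairs do not depend on the coefficient test, and together they address equality of all three time points, though with the wrong variance.
- **That the p-values are too small.** With stable differences they are too large. Reading either coefficient at 5% could raise the error towards 1 − 0.95² = 9.8% with independent visits, but the plan states no such rule.
- **That the interval for the overall action proportion is too narrow.** The protocol plans to report that proportion and specifies no interval.
- **That the Objectives 1 and 2 models would hide a dip at T2, the only remote visit.** This would follow from a linear time slope, but the protocol does not say that time is entered that way.

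The phrase about three independent levels describes the coding of the factor. It makes no claim about visits. The independence assumption comes from the model and the unpaired tests.

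**Conclusion.** The point holds on two counts that follow from the text alone: clustering by patient and physician is ignored, and a single-coefficient t-test is named for a 2-df hypothesis. The resulting p-values are not a sound basis for the p ≤ 0.05 threshold.

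The size and sign of the error rest on variance components that the protocol does not give. Under the assumptions used and at an action rate of 0.5, the error runs from strongly conservative, with loss of power, to a little more than twice the nominal level. The inflated case needs physicians who change differently over time. That is possible in a study that plans to adapt its implementation as it goes, but it is not shown. Separation matters only at action rates of about 0.9 or more, or with few visits of concern.

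This should be corrected, but it concerns a secondary outcome of a pilot and its impact is modest.

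**What to change.** In Quantitative analysis, for the service outcome:

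- Fit a logistic mixed model with a random intercept for patient and a term for physician, with time as a three-level factor.
- Test time with a joint 2-df likelihood-ratio test.
- Take the three pairwise contrasts from the same model, with Bonferroni correction, in place of the unpaired two-proportion tests.
- State in Table 3 which p-value the threshold refers to; the joint test is the natural one.
- If any time point has 0% or 100% action, use a penalised logistic fit, or report the proportions descriptively without a test. Ordinary exact intervals would again treat visits as independent.

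For the Objectives 1 and 2 models, state that time enters as a three-level factor with a joint 2-df test.

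The cost is analysis wording only; data collection and sample size do not change. The limits should be stated: with five physicians the between-physician variance is poorly estimated, and a physician intercept does not absorb physicians drifting apart over time. The p-value for this outcome should therefore be read with caution even after the change.

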## Study metrics and instruments

Details on the constructs assessed; the instruments and metrics used; the chosen thresholds for success, if applicable; the participant group contributing data; and the timing of data collection are presented in Table 2. Many of the chosen metrics are based on those recommended by Stover et al. (2020). Importantly, the authors emphasize the need to standardize evaluation metrics in patient-reported measure implementation and to distinguish between those used to assess perceptions of the innovation and those used to assess the implementation strategy. Not meeting the set thresholds for success, in this study, will signify that modifications are necessary before proceeding to a definitive trial (Thabane et al., 2010).

Table 1. Schedule of study procedures for participants

| Procedure                                                  | Timeline               |                        |                        |                        |
|------------------------------------------------------------|------------------------|------------------------|------------------------|------------------------|
|                                                            | Prior to study start   | Study start (baseline) | Month 3                | Month 6                |
| Be screened and/or consent                                 | Patients
Physicians |                        |                        |                        |
| Attend educational meeting                                 | Physicians             |                        |                        |                        |
| Receive training on the I-Score measure and Opal           | Patients
Physicians | Patients
Physicians | Patients
Physicians | Patients
Physicians |
| Complete the I-Score measure via Opal                      |                        | Patients               | Patients               | Patients               |
| Examine the I-Score measure results via the ORMS dashboard |                        | Physicians             | Physicians             | Physicians             |
| Attend HIV patient-physician visit (online or in person)   |                        | Patients
Physicians | Patients
Physicians | Patients
Physicians |
| Complete the post-visit checklist                          |                        | Physicians             | Physicians             | Physicians             |

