|                         | Ensure open channels of communication with time and space for clinicians to criticize and feedback on the PROM process | Process: Reflecting & evaluating | -                                   | Plan: Organize clinician implementation team meetings                                                                                                                                                                                                                    |
|                         | Implementation leads must consider feedback and use it to develop the process                                          | Process: Reflecting & evaluating | -                                   | Quality management: Conduct cyclical small tests of change

Building on feedback received from patients and physicians and the Application Manager's field notes, we will use a rapid-cycle evaluation approach, using the CFIR, to improve implementation. |

*Note.* PROM = patient-reported outcome measure; CFIR = Consolidated Framework for Implementation Research; \* Reproduced or adapted from Foster et al. (2018); \*\* Based on Damschroder et al. (2009); \*\*\* Based on the taxonomies of Powell et al. (2012, 2015).

Table 3. Implementation science metrics and effectiveness outcomes collected for the pilot study.

| Objective                                                                                   | Construct                 | Data collected                                                                                              | Threshold for success | Participant group |            | Timing     |
|---------------------------------------------------------------------------------------------|---------------------------|-------------------------------------------------------------------------------------------------------------|-----------------------|-------------------|------------|------------|
|                                                                                             |                           |                                                                                                             |                       | Patients          | Physicians |            |

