| Objective 3
– Determine preliminary intervention effectiveness & outcome measure utility | Patient management        | Checklist of physician actions following review of the I-Score results                                      | $p \leq 0.05$         | -                 | ✓          | T1, T2, T3 |
|                                                                                             | Barriers to ART adherence | The I-Score PROM                                                                                            | $p \leq 0.05$         | ✓                 | -          | T1, T2, T3 |
|                                                                                             | Adherence to ART          | Self-Rating Scale Item (Feldman et al., 2013)                                                               | $p \leq 0.05$         | ✓                 | -          | T1, T2, T3 |
|                                                                                             | Viral load                | The HIV RNA viral load, as indicated in the patient's medical file (> 50 copies = detectable)               | $p \leq 0.05$         | ✓                 | -          | T1, T3     |

PROM: patient-reported outcome measure; ART: antiretroviral therapy. \* Qualitative data include the Application Manager's notes (T1-T3), the qualitative interviews with patients and the focus groups with physicians (T2, T3).

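### Patient management is judged by p ≤ 0.05 on a change between T1, T2 and T3, but the I-Score is already in use at T1, so the test cannot show promise

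*Protocol*

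**What the plan says.** The service outcome under Objective 3 is patient management, recorded by the physician on a checklist after each visit. The Quantitative analysis section defines it as the proportion of visits with action based on the I-Score results, among visits where the physician identified a barrier of concern. It plans two kinds of test:

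- a logistic regression with time as a three-level factor: "We will test the null hypothesis that time has no effect on the probability of taking action", by a t-test on the regression coefficient;
- "testing the null hypothesis of equality of proportions between all pairwise combinations of time points", with a Bonferroni correction.

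The level is set once for everything: "For all analyses, a significance level of 5% will be adopted". The same paragraph also plans to report the proportions at T1, T2 and T3 and overall.

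Table 3 (the body text calls it Table 2) has a column headed "Threshold for success". In the patient-management row, whose measure is "Checklist of physician actions following review of the I-Score results", the entry is p ≤ 0.05 and nothing else. The Study metrics and instruments section attaches a consequence to such entries: "Not meeting the set thresholds for success, in this study, will signify that modifications are necessary before proceeding to a definitive trial".

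On timing, the section on the I-Score intervention has patients "complete the I-Score PROM prior to each of three consecutive visits with their HIV physician". In Table 1 the physician row "Examine the I-Score measure results via the ORMS dashboard" is marked at study start, month 3 and month 6, as is the post-visit checklist. The design has one arm.

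**The concern.** A test of T1 against later visits speaks to an intervention's effect only if T1 is free of the intervention. For physician action it is not. The physician already holds the I-Score results at T1, and the checklist asks what was done because of them at that visit. Numerator and denominator both come into being with the I-Score, so no earlier value could be collected. All three time points are intervention visits, and no control arm supplies a comparison.

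A significant time effect then means that physicians' use changed over six months. Objective 3 asks something else: whether the intervention shows promise. Evidence of promise for this outcome is that physicians act on the scores and keep doing so, which is a level and its stability. The written threshold rewards instability in either direction. Read with the general rule on unmet thresholds, a pilot in which physicians act consistently from the first visit would be marked as needing modification on this outcome.

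**Working it through.** **Inputs from the protocol.** 30 patients and 5 physicians; three visits; hence at most 30 visits per time point and 90 in all. Significance level 0.05. Nulls of no effect and of equality, with no direction stated. The protocol gives no expected action rate, no expected number of qualifying visits and no power figure for this outcome, so there is no figure to reproduce.

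**Assumptions.** Visits are independent, and there are 20 qualifying visits per time point (15 and 25 as a range). The action rates are illustrative.

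**Step 1: steady action.**
- 27/30 at each visit (90%): the proportions are equal and p = 1.00. Threshold missed.
- 3/30 at each visit (10%): p = 1.00. The same result.
- 100% at each visit: the outcome does not vary, the time coefficient cannot be estimated and the t-test is undefined. The threshold can never be met.

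**Step 2: falling action of 19/20, 15/20, 11/20.**
- Coefficient for T3 against T1 (Wald): the log odds ratio is ln(11/9) − ln(19/1) = 0.201 − 2.944 = −2.744. SE = √(1/19 + 1/1 + 1/11 + 1/9) = √1.2546 = 1.120. z = −2.45, p = 0.014.
- Likelihood ratio, 2 df: the pooled rate is 45/60, so 15 actions and 5 non-actions are expected at each visit. G² = 2[19 ln(19/15) + 1 ln(1/5) + 11 ln(11/15) + 9 ln(9/5)] = 2 × 4.760 = 9.52; the T2 terms are zero. p = exp(−4.760) = 0.009.
- Bonferroni t-test, T1 against T3: p = 0.008.

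All three meet p ≤ 0.05. The mirror-image rise 11/20, 15/20, 19/20 gives identical p-values, because each statistic depends on the size of the difference and not on its sign.

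**Step 3: how often the threshold is met (simulated trials).** Table 3 does not say which test its p-value refers to, so three readings are shown. Where the coefficient could not be estimated, the trial counts as not significant.

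| True rates T1/T2/T3 | Visits per time point | T3 vs T1 coefficient (Wald) | Bonferroni pairwise | Likelihood ratio, 2 df |
|---|---|---|---|---|
| 95/75/55% | 15 | 25% | 67% | 72% |
| 95/75/55% | 20 | 51% | 78% | 84% |
| 95/75/55% | 25 | 66% | 90% | 92% |
| 95/85/75% | 20 | 10% | 30% | 42% |
| 95/95/95% | 20 | about 0% | under 1% | about 5% |

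The coefficient test and the pairwise tests are the ones the protocol names. The likelihood-ratio test is the usual single test of a three-level factor, but the protocol does not mention it.

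**The case against.** Several points on the other side stand. Patient management is a secondary-objective outcome, and the Study design section describes a type 3 hybrid as one that only observes effectiveness data. The Quantitative analysis section links its score targets for going on to a definitive trial to Objectives 1 and 2, so the tie between this cell and progression is looser than for acceptability or feasibility. The general sentence on unmet thresholds makes no exception for Objective 3, however, and a p-value in a success column is more than observation.

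The proportions per visit and overall are already to be reported, so sustained action or decline would be visible in the results. A reader might infer that the protocol would hide a decline or declare it a success. It does neither: no sentence calls a fall a success, and the reported proportions would show it. The defect is narrower, in that the written threshold does not exclude a fall.

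The missing direction is not special to this row, since all four Objective 3 rows carry the same bare p ≤ 0.05. What is special here is the absence of a pre-intervention value. A reader might extend that to barriers to adherence, but the T1 barrier score is taken before the first visit informed by the I-Score and can serve as a baseline.

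The time test also has a use. Peripheral components and the implementation strategy may be adapted during the study through plan-do-study-act cycles, and a change in physician action is relevant to that. This supports keeping the test, not using it as the success rule.

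Finally, 84% should not be taken as the chance that a decline passes. It depends on the test, on a 40-point fall and on 20 visits per time point. With a 20-point fall, the pass rates are 10% to 42%.

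**Conclusion.** The point holds for the success criterion, not for the whole planned analysis of the service outcome. The p ≤ 0.05 entry for patient management can only refer to differences among T1, T2 and T3, all of which are intervention visits, so it cannot say whether the intervention shows promise. Three consequences follow without any assumption about rates: constant high and constant low action get the same result, action at every visit cannot meet the threshold, and a fall counts the same as an equal rise under the undirected tests as written.

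The frequencies are illustrative. They rest on assumed visit numbers and rates, and on independence between visits that in fact share 30 patients and 5 physicians. Under them, a fall from 95% to 55% meets the threshold in about half to five-sixths of trials at 20 visits per time point, and steady 95% action in about 0% to 5%.

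This should be fixed, but it is not critical. The primary outcome, acceptability, and the other Objective 1 and 2 thresholds are unaffected.

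**What to change.** 1. In Table 3, Objective 3, remove p ≤ 0.05 from the patient-management row. A dash would do, as used there for the rate of technical issues. If the sponsor wants a threshold, it should be a target proportion of the sponsor's choosing.
2. In the Quantitative analysis section, state that the outcome is judged on the proportions already planned, per visit and overall, each with a 95% confidence interval that allows for repeated visits of the same patient and physician. For orientation, exact intervals that ignore clustering are 73.5% to 97.9% for 27/30 and 81.9% to 95.3% for 81/90.
3. In the same paragraph, state that T1 is an intervention visit for this outcome, and that the time tests describe sustainment or adaptation of use and are not a success criterion.

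The cost is one table cell and two or three sentences, with no change to data collection. The downside is that the service outcome can no longer support a claim of statistical significance.
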